### Education

2.9

Within each of the five AEP intervention consultations, there will be a discussion incorporating an educational topic about the role of exercise in childhood cancer. This will be delivered using video and written information resources and discussions on the topic which will be addressed to the parent, with age-appropriate language tailoring to the participant. This will facilitate further learning on behaviour change techniques and key exercise principles in cancer care. The education topics include (1) Principles of Exercise and Cancer, (2) Graded exercise: how to progress and regress, (3) Activity pacing for fatigue, (4) Digital technology and local programs, and (5) a topic chosen by participant from: managing peripheral neuropathy, social support, long-term maintenance, and self-monitoring physical activity. These education topics were developed by engaging with consumer families, and designed to build self-efficacy to equip participants with the behaviour change techniques to apply in their daily life, in line with the study primary aim. Specific skills learnt include self-monitoring, barrier management, planning, goal setting, growing social support, and building confidence and belief in their own ability to be physically active.

### Control group

2.10

The control group will not receive an individualised exercise program during the control period, but instead will be emailed educational resources about the importance of physical activity after allocation into the control group including online resources developed by Exercise and Sport Science Australia [44] and the International Pediatric Oncology Guidelines [45]Control group participants will be offered a delayed-start opportunity to participate in the intervention after the 24 week follow-up (T2) assessment. This approach allows for ethical treatment and addresses any potential concerns about withholding treatment.

### Assessing implementation: the reach, effectiveness, adoption, implementation, and maintenance (RE-AIM) framework

2.11

The reach, effectiveness, adoption, implementation, and maintenance (RE-AIM) framework will be used to evaluate the implementation of the MERRIER study into a community organisations usual operations from individual (i.e., survivors and families) and organisational levels [46]. Reach will be measured by the calculating the proportion and characteristics of individuals who were eligible and able participate, as well the proportion excluded and reasons for exclusion. Effectiveness measures of the co-primary outcomes (self-efficacy and objectively measured moderate-vigorous physical activity), and secondary outcomes (e.g., patient-reported outcomes and physical assessments) for group changes will be conducted between baseline (T0) and post-intervention (T1). Adoption will be measured by calculating the number of enrolled and completed participants by the total eligible, while qualitative interviews with research staff will be conducted iteratively to understand reasons for non-recruitment and drop-out mid-way through recruitment. Implementation will be measured by calculating the adherence (percentage of prescribed exercises completed) and compliance (percentage of exercise intervention consultations completed, and number of participants who complete >70 ​% of their prescribed exercises using the Physitrack exercise software), and listing adaptations made to the intervention during the study. Maintenance will be a measure of the co-primary and secondary outcomes at post-intervention (T1) and 24-week follow-up (T2) (i.e. >60 ​% of participants report a self-efficacy score and physical activity minutes (using self-report) equal to or higher than their baseline score at the 24-week follow-up (T2)). Fidelity checks will be carried out to ensure consistency and safety in the delivery of the online exercise intervention. Consultations will be recorded using Microsoft Teams and stored on a secure password-protected cloud-based network at The University of Sydney for quality assurance. Ten percent of exercise consultations will be randomly reviewed to observe and improve program delivery.

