### Aims

1.1

This trial is a type 1 hybrid effectiveness-implementation trial designed to:1)Determine the effectiveness of the MERRIER intervention, an exercise program delivered online to childhood cancer survivors in conjunction with a community organisation, in improving moderate-vigorous physical activity levels and physical activity self-efficacy.2)Examine the factors that may increase the program reach, effectiveness, adoption, implementation and maintenance

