### Randomization

2.3

Following the completion of baseline (T0) assessments including physical assessments, questionnaires and 5-day objective physical activity wrist-worn accelerometry, participants will be assigned to either the exercise intervention or control group (Fig. 1). Randomization will occur in a 1:1 ratio using the online computer-generated randomisation software, Sealed Envelope, which will be completed by an independent researcher outside the core study team. Randomisation will be performed in blocks to ensure balance across important variables, including age (categorized into three groups: 5–9, 10–13, and 14–18), sex (male, female), and disease type (liquid, solid, brain tumours).

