### Sample size

2.13

In this study, a sample size of 52 patients is required to achieve 90 ​% power to detect a significant difference (p ​< ​0.05) of 10 ​min/day difference in moderate-vigorous physical activity measured using the Axivity AX3 accelerometer between the experimental and control groups at post-intervention (T1). This calculation was conducted using the Sealed Envelope™ online Power Sample Size Calculator tool [48], assuming a standard deviation of 11 ​min/day and a 15 ​% drop-out rate. Therefore, this study will enrol 60 childhood cancer survivors.

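### Two unranked co-primary outcomes rest on a sample size built for one: the 90% power holds for accelerometer MVPA alone, not for a trial with two co-primaries

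*Protocol article*

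**What the plan says.** Section 1.1 gives one effectiveness aim covering two outcomes: whether the program works "in improving moderate-vigorous physical activity levels and physical activity self-efficacy". Section 2.11 makes both primary, speaking of "Effectiveness measures of the co-primary outcomes (self-efficacy and objectively measured moderate-vigorous physical activity", compared between baseline and T1. It uses the co-primary label again under maintenance. Section 2.9 also links building self-efficacy to the primary aim. Neither outcome is placed above the other.

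The sample size in section 2.13 concerns one of them only. It is set for 90% power at p < 0.05 to find a 10 min/day "difference in moderate-vigorous physical activity measured using the Axivity AX3 accelerometer between the experimental and control groups at post-intervention (T1"), "assuming a standard deviation of 11" min/day. It arrives at 52, and 60 after a 15% drop-out allowance. Section 2.6.1 describes the PASES instrument but gives no difference to detect and no standard deviation. Section 2.14 plans generalised linear mixed models and does not say how the two co-primaries combine into a conclusion.

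**The concern.** When two outcomes have equal primary standing, the false-positive rate and the power of the trial depend on what counts as success: either outcome, both, or one before the other. The sample size was calculated as if there were a single primary outcome with the full 5% available to it.

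The two outcomes also differ in how easily they can be biased. PASES is a questionnaire, and section 2.6 allows parental help or proxy completion. Families will know whether they received five consultations, equipment and a voucher (section 2.8) or emailed resources (section 2.10). Without a ranking, a positive PASES result beside a null accelerometer result could be reported as success on a primary outcome. Conversely, a real MVPA effect could be discounted because PASES, which was never powered, did not reach significance.

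**Working it through.** **Inputs.** From section 2.13: difference 10 min/day, SD 11 min/day, p < 0.05, power 90%, drop-out 15%, 52 required, 60 enrolled. From section 2.3: "Randomization will occur in a 1:1 ratio". Sidedness is not stated; I take two-sided, because it reproduces the plan's figure and one-sided does not (21 per arm, 42 in total). The PASES effect sizes and the correlation between the two test statistics are my assumptions, shown as ranges.

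**1. The plan's figure.** n per arm = 2 × (1.96 + 1.2816)² × (11/10)² = 25.4, rounded up to 26, so 52 in total. This matches, and it shows that the full 0.05 was spent on MVPA. Power at 26 per arm: 10 / (11 × √(2/26)) = 3.278; Φ(3.278 − 1.960) = 90.6% (89.5% with the t distribution). With 60 enrolled and 15% lost, 51 remain and power is 90.1%.

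**2. Either outcome may win, each at 0.05.** Chance of at least one false positive if independent: 1 − 0.95² = 9.75%. From the bivariate normal: 9.5% at correlation 0.3, 9.1% at 0.5, 7.8% at 0.8.

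**3. Alpha split, 0.025 each.** The critical value rises to 2.241, so MVPA power at 52 is Φ(3.278 − 2.241) = 85.0%, and 84.2% at 51. To restore 90%: 2 × (2.241 + 1.2816)² × 1.21 = 30.0, just over 30, so 31 per arm, 62 evaluable, and 62/0.85 = 73 enrolled.

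**4. Both must win, each at 0.05.** The 5% error rate holds and MVPA alone keeps its 90%. Joint power at 52 evaluable:

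| Assumed PASES standardised effect | PASES power alone | Joint power, correlation 0 | Joint power, correlation 0.5 |
|---|---|---|---|
| 0.91 (same as MVPA, 10/11) | 90.6% | 82.1% | 84.2% |
| 0.80 | 82.2% | 74.5% | 77.4% |
| 0.65 | 64.9% | 58.8% | 62.3% |
| 0.50 | 43.8% | 39.7% | 42.6% |

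The first row at correlation 0 is 0.906 × 0.906 = 0.821. With an effect of 0.91 on both outcomes, 90% joint power would need 62 to 64 evaluable, or 73 to 76 enrolled.

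**5. Fixed order, MVPA first.** MVPA is tested at the full 0.05 with its 90.6% power, and the family-wise error stays at 5%. PASES can be claimed only when both tests are significant, so its chance of being claimed is the joint power in step 4.

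All power figures in steps 2 to 5 use the normal approximation for a two-group comparison. The planned mixed models could do somewhat better by using the baseline values.

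**The case against.** The strongest reply is that section 2.13 is not wrong. It claims 90% power for a "min/day difference in moderate-vigorous physical activity measured using the Axivity AX3 accelerometer between the experimental and control groups" and nothing more. A both-must-win rule leaves that claim and the 5% intact, and so does an MVPA-first order. A reader might infer that no meaning of co-primary lets both stated properties stand; the documents do not support this, since two ordinary decision rules satisfy both. This part of the reply stands in full.

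A reader might also take the 9% to 10% as the risk of the pattern described above, PASES significant and MVPA null. It is not. It is the chance of any false positive on either outcome in either direction. When neither outcome has an effect, that specific pattern has probability 9.75% − 5% = 4.75% if independent, and 9.1% − 5% = 4.1% at correlation 0.5. Nor does the article adopt the either-wins rule; that is one of several possibilities it leaves open.

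The second reply is that multiplicity rules are commonly left to the statistical analysis plan, which is not at hand. That is fair as to the rule itself, and the absence of a rule is not the point here. But the article fixes both the equal standing of the two outcomes and a sample size resting on one of them. A later analysis plan that split alpha or required both outcomes could not recover the lost power at 60 enrolled, and one that ranked MVPA first would alter the hierarchy in section 2.11.

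Finally, section 2.1 calls the effectiveness evaluation preliminary. That lowers the weight of the point without removing it, because section 2.13 still describes a formal significance test with 90% power.

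**Conclusion.** The point holds in a limited form. The 52 and the 90% are correct for MVPA alone. They do not describe a trial with two co-primaries of equal rank, and PASES has no power statement of any kind. Depending on the decision rule, the cost is a family-wise error of 9.1% to 9.75% (correlation 0.5 to 0), a fall in MVPA power of about 5 to 6 points to 85.0%, or joint power below 90%.

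The error rates and the MVPA power follow from the document's own inputs, taking the test as two-sided. The joint-power figures rest on assumed PASES effects, because the article gives none, so they show a range and are not estimates. The severity is moderate: the aim is stated as preliminary effectiveness, and the remedy is wording.

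**What to change.** Before any outcome data are analysed, state in sections 2.11 and 2.13 that effectiveness is tested in a fixed sequence: MVPA at T1 first at two-sided 0.05, then PASES at T1 at two-sided 0.05 only if MVPA is significant. PASES can remain a second-ranked primary outcome or become the key secondary, so self-efficacy need not leave the aims. Say in section 2.13 that the sample size and the 90% refer to MVPA only and that PASES is not powered. Align sections 1.1 and 2.9 and any registered outcome hierarchy with this, and date the change, since recruitment was planned from March 2025.

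This keeps 60 participants, the 5% error rate and the stated MVPA power. The price is that PASES cannot be claimed confirmatorily if MVPA fails.

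If equal standing matters more to the investigators, a both-must-win rule or an alpha split would also settle the question. In that case the lower power shown above should be reported, or enrolment raised to about 73 for the split, or to 73 to 76 for both-must-win under the equal-effect assumption.

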### Semi-structured interviews

2.12

Semi-structured interviews in a sub-set of participants (n ​= ​10 parent and participant dyads) and research and community organisation staff (n ​= ​5) will be conducted using the Consolidated Framework for Implementation Research (CFIR) to identify barriers and enablers to program implementation (e.g. reasons for (or lack of) program maintenance, adherence) [47]. Interview outcomes will aim to understand adoption of the intervention at the setting level, understand staff participation, adaptations required, and whether the program (or specific components) were adopted in the long-term (at the follow-up (T2) timepoint, i.e. 3 months after completion of the program). Purposive sampling will be conducted to ensure diversity of age, gender, ethnicity, activity level, as well as cancer diagnosis for participants. Interviews will be conducted either online using Microsoft Teams or via telephone with trained study staff.

### Sample size

2.13

In this study, a sample size of 52 patients is required to achieve 90 ​% power to detect a significant difference (p ​< ​0.05) of 10 ​min/day difference in moderate-vigorous physical activity measured using the Axivity AX3 accelerometer between the experimental and control groups at post-intervention (T1). This calculation was conducted using the Sealed Envelope™ online Power Sample Size Calculator tool [48], assuming a standard deviation of 11 ​min/day and a 15 ​% drop-out rate. Therefore, this study will enrol 60 childhood cancer survivors.

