### Objective physical activity levels

2.7

Average daily minutes of moderate-vigorous physical activity will be objectively measured using an Axivity AX3 accelerometer. The Axivity AX3 accelerometer is a research-grade waterproof wrist accelerometer that records continuous daily activity and captures acceleration along three axes (x, y, and z) with a sample frequency of 100 ​Hz. It shows good validity and accuracy at both wrist locations (ICC of 0.91 for comparison of left and wright wrists) [40], and validated with other research grade accelerometers with an ICC of 0.95 [41]. Participants will be instructed to attach the Axivity AX3 accelerometer on their non-dominant wrist for 5 consecutive days (including two weekend days and evenings). To be included for weekly physical activity calculations, at least four valid days are required. Valid days are defined as wearing the accelerometer for at least 10 ​h/day [40] with non-wear time being defined as not wearing the accelerometer for 60 consecutive minutes [41]. Accelerometer data will be collected at the start and end of the intervention. Participants will be provided with instruction on how to wear the accelerometer and will be provided with postage paid return envelopes for baseline (T0) and post-intervention (T1). Once returned to the researchers, participant data will be immediately downloaded onto a password protected computer.

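### Section 2.13 multiplies by 1.15 where it should divide by 0.85: 60 enrolled with 15% loss leaves 51, not 52, with no margin for invalid accelerometer wear

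*Protocol article*

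**What the plan says.** Protocol article, section 2.13 (Sample size), states that "a sample size of 52 patients is required to achieve 90" per cent power at p < 0.05 for a 10 min/day difference in accelerometer-measured moderate-vigorous activity between groups at post-intervention (T1), "assuming a standard deviation of 11" min/day and 15% drop-out. It ends: "Therefore, this study will enrol 60 childhood cancer survivors".

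Section 2.7 (Objective physical activity levels) has the device worn for five consecutive days and counts a day as valid at 10 hours of wear or more. It then sets the inclusion rule: "To be included for weekly physical activity calculations, at least four valid days are required".

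Section 2.3 (Randomization) places 1:1 allocation as follows: "Following the completion of baseline (T0) assessments including physical assessments, questionnaires and 5-day objective physical activity wrist-worn accelerometry". It neither requires nor rules out a check that this wear met the four-day rule. Section 2.7 says that data are downloaded as soon as a device is returned.

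**The concern.** The three figures in section 2.13 (52 required, 15% lost, 60 enrolled) do not fit together. If 15% are lost, 60 enrolled children do not yield 52.

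The 52 must also be children with usable T1 accelerometer data, because that is the outcome the calculation is built on. A child can complete the trial and still be excluded from it by having two short days out of five. Section 2.13 names only drop-out, so a reader cannot tell whether this second kind of loss is inside the 15%. If it is outside, it comes off a number that is already one short.

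What is at stake is the stated 90% power on one of the two co-primary outcomes. At baseline there is a related, avoidable gap: a child may be randomised after finishing the five days without having a usable baseline value.

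**Working it through.** **Inputs.** Difference 10 min/day, SD 11 min/day, alpha 0.05, power 90%, drop-out 15%, enrolment 60 (section 2.13); 1:1 allocation (section 2.3); at least four valid days of five (section 2.7). Sidedness is not stated. Two-sided reproduces the protocol's figure, while one-sided would give 42.

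**1. Reproduce 52.** Normal approximation, two-sided:

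n per arm = 2 × SD² × (1.960 + 1.282)² / difference² = 2 × 121 × 10.507 / 100 = 25.43, so 26 per arm and 52 in total.

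This matches exactly with no drop-out in it, so 52 is the number before loss. (A t-test needs 26.43, so 27 per arm and 54 in total.)

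**2. Reproduce 60.**
- 52 × 1.15 = 59.8, so 60. This is the stated enrolment.
- 52 / 0.85 = 61.2, so 62 in 1:1 pairs. This is the enrolment that 15% loss requires.

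**3. What 60 delivers.**
- 60 × 0.85 = 51 evaluable.
- Largest loss that still leaves 52: 1 − 52/60 = 13.3%.

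**4. Power at each evaluable total N.** Normal approximation: Φ[(10/11) × √(N/4) − 1.960]. For N = 51 this is Φ(3.246 − 1.960) = Φ(1.286) = 90.1%. The t-test column uses the same standardised difference, 10/11 = 0.909.

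| Evaluable | Normal | t-test |
|---|---|---|
| 52 | 90.6% | 89.5% |
| 51 | 90.1% | 88.9% |
| 50 | 89.5% | 88.3% |
| 47 | 87.6% | 86.2% |

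Going from 52 to 51 costs 0.5 to 0.6 percentage points. By the protocol's own formula, 51 is the last total at or above 90%; 50 falls below it.

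**5. Invalid wear.** The documents give no rate, so this step is an assumption. If 2% of the 51 fail the four-day rule, 51 × 0.98 = 50 remain; if 8% fail, 51 × 0.92 = 46.9, so 47 remain. Power is then 89.5% to 87.6% (normal) or 88.3% to 86.2% (t-test). No credit is taken for baseline adjustment.

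**The case against.** The strongest reply is that the slip costs almost nothing. The formula that gives 52 still gives 90.1% at 51, so the stated 90% survives. The 88.9% appears only on switching to a t-test, under which even 52 gives 89.5%. This stands, and it is why the arithmetic alone is a minor correction.

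Second, a reader might infer that invalid wear was left out of the 15%. The text does not establish that: drop-out is not defined in section 2.13, and the full protocol may define it. What stands is that the section does not say, and that even if the 15% covers both losses, 60 still leaves 51.

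Third, a reader might expect a much larger loss of power by assuming that many days fail, or by requiring valid wear at both T0 and T1. The documents support neither. They give no invalid-day rate, and the device is a waterproof wrist monitor that needs only 10 hours a day. Section 2.13 sizes the trial on the T1 difference, and section 2.14 plans mixed models over time, which can keep a child with only one valid timepoint.

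Fourth, adjusting for baseline could recover precision. That is fair, though neither the baseline-to-T1 correlation nor the meaning of the SD of 11 (raw T1 values or change) is given, and section 2.13 claims no such gain.

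**Conclusion.** The point holds in a limited form. The inflation in section 2.13 is wrong by two children (60 against 62), and 60 enrolled with 15% loss leaves 51. On its own this leaves power at 90.1% (normal) or 88.9% (t-test), so it does not undermine the trial.

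It matters because it uses up all the margin on an outcome with its own exclusion rule, whose losses section 2.13 does not mention. One further unusable record takes power to 89.5% by the protocol's own formula. Under an assumed 2% to 8% failure of the wear rule, the cost relative to 51 is about 0.6 to 2.5 percentage points by that formula. The loss figures are certain arithmetic; the size of the invalid-wear loss is not, because it rests on an assumed rate. The correction is cheap and worth making.

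**What to change.** (a) Restate section 2.13: 60 enrolled covers 13.3% loss from all causes, including children who fail the valid-wear rule; at 15% loss 51 remain, with power of about 89% to 90%. This costs one or two sentences and no additional children.

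(b) In section 2.3, add a check before randomisation that the returned T0 device shows at least four valid days, and allow one repeat wear if it does not. The data are already downloaded on return, so the check itself adds little work. The cost is a short delay to allocation for the children who repeat. Section 2.8 places the first consultation within two weeks of the baseline assessment, so the repeat has to be fitted to that window.

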### Statistical analysis

2.14

Descriptive statistics will be used to summarise participant demographic factors of age, sex, rural/urban, primary diagnosis of cancer, comorbidities, treatment received, as well as RE-AIM domains. We will perform generalised linear mixed models to evaluate effectiveness changes in outcome measures over time. To deal with the variance in effectiveness of implementation, we will employ multilevel modelling to examine differences in relation to reported physical activity levels and adherence to the exercise intervention by age. Quantitative data will be analysed using IBM SPSS software (Version 26.0, IBM Corp., Armonk, NY). Qualitative data will be transcribed using Microsoft Teams, imported into NVivo Version 12 for coding, and thematically analysed following Braun and Clarke's six-step framework [49]. Two independent authors will code the data to ensure reliability, with discrepancies resolved through discussion or consultation with a third researcher, if necessary. The analysis will be conducted iteratively, allowing for themes to emerge inductively from the data while considering deductive insights from the study objectives [50].

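### The trial is sized on the between-arm MVPA difference at T1, but section 2.14 states effectiveness only as change over time; the arm contrast and the use of baseline should be fixed

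*Protocol article*

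**What the plan says.** Four sections of the protocol article bear on this.

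- **2.13 Sample size** asks for 52 children for 90% power to detect 10 min/day in MVPA, compared "between the experimental and control groups at post-intervention (T1", and it does so "assuming a standard deviation of 11" min/day. After an allowance for drop-out, 60 are enrolled.
- **2.11 RE-AIM framework** says that effectiveness analyses of the co-primary outcomes (self-efficacy and objectively measured MVPA) and the secondary outcomes "for group changes will be conducted between baseline (T0) and post-intervention (T1").
- **2.14 Statistical analysis** has one sentence on the effectiveness model: "We will perform generalised linear mixed models to evaluate effectiveness changes in outcome measures over time". It names no arm term, arm-by-time term or T1 contrast, and does not mention baseline values or the randomisation factors. Age appears only in a separate multilevel model of reported activity and adherence.
- **2.3 Randomization** says: "Randomisation will be performed in blocks to ensure balance across important variables, including age". The other two factors are sex and disease type. With three age groups, two sexes and three disease types there are 18 cells.

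MVPA by accelerometer is measured at T0 and T1 only (2.4 and Table 1). PASES, the other questionnaires and the physical tests are measured at T0, T1 and T2.

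**The concern.** Aim 1 asks about the effect of the programme, and in a randomised trial the contrast between arms answers that. Change over time within an arm also carries recovery after treatment, growth and season in children aged 5 to 18. The sample size section names the arm contrast; the analysis section does not.

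The silence also leaves open which longitudinal parametrisation is meant. One common default, a group-by-time interaction with a separate baseline mean in each arm, amounts to comparing change scores when there are two time points. That comparison is less precise than a baseline-adjusted one at any r below 1. When r is below about 0.5 it is also less precise than the plain T1 comparison used to size the trial. With 52 evaluable children planned, this decides whether the stated power is kept.

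**Working it through.** **Inputs from section 2.13:** difference 10 min/day, SD 11 min/day, alpha 0.05, power 90%, 52 evaluable (26 per arm). Section 2.3 gives 1:1 allocation. Sidedness is not stated; two-sided is used because it reproduces the stated size.

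**Assumptions not in the article:** 11 is the SD of the T1 value and is the same at T0; r is the T0–T1 correlation of MVPA, taken over a range.

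**1. The plan's own figure.** Per arm, n = 2 × (1.96 + 1.2816)² × 11² / 10² = 25.4, rounded up to 26, so 52 in total. This matches exactly. No baseline correlation enters, so the trial was sized on an unadjusted two-sample comparison. One-sided testing would give 21 per arm and does not match. At 26 per arm the power is 90.6% by the normal approximation and 89.5% by the t-test.

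**2. SD under each analysis.**

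- Unadjusted T1 comparison: 11.
- Baseline-adjusted T1 contrast (ANCOVA): 11 × √(1 − r²).
- Change score, or unconstrained group-by-time contrast: 11 × √(2(1 − r)).

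**3. Variance ratio, change against adjusted:** 2(1 − r) / (1 − r²) = 2/(1 + r).

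**4. Results**, t-test power with 26 per arm and difference 10:

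| r (assumed) | Adjusted SD | Adjusted power | Change SD | Change power | Variance ratio |
|---|---|---|---|---|---|
| 0.3 | 10.49 | 92.1% | 13.02 | 77.5% | 1.54 |
| 0.5 | 9.53 | 96.0% | 11.00 | 89.5% | 1.33 |
| 0.7 | 7.86 | 99.4% | 8.52 | 98.6% | 1.18 |

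At r = 0.5 the change SD equals 11, so the change contrast has the power of the unadjusted T1 comparison; below that it has less. By the normal approximation, 90% power at r = 0.3 needs 72 evaluable children for the change contrast and 48 for the adjusted one, against the planned 52.

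**5. A common baseline mean.** A mixed model with T0 and T1 as responses and one baseline mean for both arms has about the precision of ANCOVA. If that is what section 2.14 means, the loss is nil.

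**6. If 11 is instead the SD of change.** The change contrast then has its planned power at any r. The adjusted SD is 11 × √((1 + r)/2), which gives 34, 40 and 44 evaluable children at r = 0.3, 0.5 and 0.7 (normal approximation). Adjustment still helps, but there is no shortfall.

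**7. Randomisation factors.** The article gives no variance explained by age group, sex or disease type, so the gain from including them cannot be computed. With 60 children in 18 cells (60/18 = 3.3 per cell), only main effects are practical.

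**The case against.** The strongest reply is that section 2.14 is a one-sentence summary in a journal article. Covariate lists and model parametrisation are commonly left to the full protocol or SAP, which are not shown. This stands: a reader might infer that the model leaves out baseline and the randomisation factors, but no section says so.

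A reader might also infer that precision is certainly being lost. That does not follow. A mixed model over T0 and T1 already uses the baseline measurement, and with a common baseline mean it gives up nothing. Even an unadjusted T1 comparison essentially meets the planned 90%, so missing covariates alone create no power shortfall.

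Nor do sections 2.11 and 2.13 conflict in what they estimate. Under randomisation, the between-arm difference in change and the between-arm difference at T1 have the same expected value and differ only in precision. And nothing in the article says that within-arm change will be read as effectiveness; the randomised design and control group point the other way.

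What the reply does not remove is that the analysis section, as worded, ties effectiveness to change over time and omits the arm contrast on which the trial was sized. The parametrisations compatible with that wording do not all keep the planned power.

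**Conclusion.** The point holds as a conditional one. Sections 2.13 and 2.14 do not name the same quantity, and 2.14 leaves room for an analysis with 1.54, 1.33 or 1.18 times the variance of the baseline-adjusted T1 contrast at r = 0.3, 0.5 or 0.7. Under that analysis power falls below the planned 90% when r is under about 0.5.

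This rests on an assumed r, on reading 11 as the SD of the T1 value, on equal SDs at T0 and T1, and on an unconstrained group-by-time fit. If baseline means are constrained equal, no precision is lost and only the missing statement of the arm contrast remains. The remedy uses only data already collected, so the change should be made whichever parametrisation was intended.

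**What to change.** State in section 2.14:

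- The primary estimate for each co-primary outcome is the intervention-minus-control difference at T1.
- **MVPA (T0 and T1 only):** either ANCOVA of the T1 value with baseline MVPA as covariate, or a mixed model with T0 and T1 as responses and baseline means constrained equal. Do not combine baseline as covariate with T0 as a response. With baseline as covariate only one visit remains as a response, so a time or arm-by-time term cannot be estimated.
- **PASES and other outcomes measured at T0, T1 and T2:** the constrained-baseline mixed model, or baseline as covariate with T1 and T2 as responses.
- Age group, sex and disease type enter as main effects only.
- Within-arm changes are descriptive.

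Section 2.13 should also say whether 11 min/day is the SD of the T1 value or of change. The cost is protocol or SAP wording: the baseline values and randomisation factors are already collected at T0, and no extra data or children are needed.
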